### Outcome Measures

The electronic questionnaires will be made accessible to all participants on each group's Facebook page with a URL link or on the CHEO webpage for those who do not wish to create a Facebook account. Participants in groups A, B, and C will be emailed the same URL link to access the questionnaires. Using the *wall* on the Facebook page for all groups, or the CHEO webpage, the research team will provide updates and reminders to all participants regarding deadlines to complete the questionnaires.

The following outcome measures will be used to answer the primary objective:

Feasibility will be assessed by the recruitment rate, the randomization process, and self-reported adherence and measured using a questionnaire, as well as protocol deviations, dropout rates, and percentage of missing data in the questionnaires.Recruitment rate: The number of participants recruited in the trial and the time used for recruitment will be documented in a feasibility form. The number of participants will be divided by the duration of recruitment. This will be measured on a continuous basis for up to 12 weeks.Randomization process: The ease at which the randomization process is conducted will be described by researchers in a feasibility form. This will be measured on a continuous basis for up to 12 weeks.Number of protocol deviations: The number of protocol deviations, the time at which they occur, the group in which they occur, and the potential reasons for these will be documented in a feasibility form. Participants will be asked why they deviated from the protocol by researchers using a feasibility form. This will be measured on a continuous basis for up to 12 weeks.Dropout rates: The number of participants who dropped out of the trial, the time at which they dropped out, the group in which they belonged, and the reasons for these will be documented in a feasibility form. Participants will be asked why they dropped out by researchers. The number of dropouts in each group will be divided by the duration of the trial. This will be measured on a continuous basis for up to 12 weeks.Percentage of missing data in the questionnaires: The percentage of missing data in the questionnaires, the time at which they occur, and potential reasons for these will be documented in a feasibility form. This will be measured on a continuous basis for up to 12 weeks.Self-reported adherence: Self-reported adherence to the training programs will be assessed by monitoring the number and length of sessions and dividing the time spent performing the program by the duration of prescribed sessions of either yoga or aerobic dance. Self-reported adherence will be recorded weekly using an adapted online version of the validated 7-day PA Report calendar (in minutes) [62]. This will be measured each week for up to 12 weeks.The acceptability of the yoga or aerobic dance interventions will be assessed using a questionnaire-administered postintervention. Questions will explore the acceptability of online consultations, virtual group sessions, PA videos (either yoga or aerobic dance programs), electronic pamphlet, and training programs (content and duration of the yoga and aerobic dance programs), as well as facilitators and barriers to participating. This questionnaire will be administered at 6 and 12 weeks.The usability of Facebook will be assessed by the System Usability Scale (SUS) [63,64]. The SUS is composed of 10 items using a 5-point scoring system ranging from Strongly Disagree (a score of 1 out of 5 for each question) to Strongly Agree (a score of 5 out of 5 for each question). The total score ranges from 5 (low usability) to 50 (high usability). The usability will be measured at 6 and 12 weeks.The usability of the videoconferencing platform will be assessed by the SUS [63,64]. The SUS is composed of 10 items using a 5-point scoring system ranging from Strongly Disagree (a score of 1 out of 5 for each question) to Strongly Agree (a score of 5 out of 5 for each question). The total score ranges from 5 (low usability) to 50 (high usability). The usability will be measured at 6 and 12 weeks.The use of Facebook will be assessed by the number of posts, live online discussions, and views of the videos. The use will be measured at 6 and 12 weeks.

The following outcome measures will be used to answer the secondary objective:

*Pain intensity* will be assessed using the electronic Childhood Health Assessment Questionnaire (CHAQ) 100-mm pain VAS subscale [65]. It uses a scoring system where 0 mm represents no pain and 100 mm represents very severe pain the past week. This measure has already been validated in the JIA population [65,66]. Pain intensity will be measured at baseline, 6 weeks, and 12 weeks.*Participation in PA (level of PA)* will be assessed by using the electronic Physical Activity Questionnaire for adolescents (PAQ-A) aged 14 to 18 years, a 7-day recall instrument measuring the level of PA within the last 7 days [67-69]. The PAQ-A is composed of 8 items using a 5-point scoring system. The total score is calculated by taking the mean score out of 5, with 1 indicating low PA and 5 indicating high PA. The PAQ-A has been reported to be a valid and reliable measure of general PA levels in youths and adolescents [67-69]. Participation in PA will be measured at baseline, 6 weeks, and 12 weeks.*Participation in PA (duration and intensity)* will be assessed by using an exercise log, based on the 7-day PA Recall calendar [62], which will be used weekly. The PA level will be reported in terms of minutes and intensity levels (3 subscales: moderate, hard, and very hard intensity; subscale total scores in minutes) and will be transformed into the metabolic equivalent of tasks, which are units of the basal metabolic rate and express the energy cost of PA. Participation in PA will be measured at baseline, 6 weeks, and 12 weeks.*Morning stiffness* will be assessed by using electronic self-reported questions asking about the presence (Yes/No) and duration of morning stiffness in minutes. It will be measured at baseline, 6 weeks, and 12 weeks.*Functional status* will be assessed using the electronic CHAQ. The CHAQ contains 8 domains (dressing/grooming, arising, eating, walking, hygiene, reach, grip, and activities), and items are scored using a 4-point Likert scale of 0 to 3, where 0 represents the ability to perform the activity with no difficulty, 1 represents the ability to perform with some difficulty, 2 represents the ability to perform with much difficulty, and 3 represents the inability to perform over the past week. The mean of the 8 scores will determine the total CHAQ score ranging from 0 to 3, with a lower score indicating higher functional status and a higher score indicating lower functional status. It is the most widely used functional health status measure in JIA, which is a reliable and valid tool for the functional, physical, and psychosocial assessment of children with JIA [65]. It will be measured at baseline, 6 weeks, and 12 weeks.*Fatigue* will be assessed by using an electronic version of a subset of the Patient-Reported Outcomes Measurement Information System Pediatric Short Form version 1.0—Fatigue 10a [70], which measures fatigue and its impact, scored from 1 to 5, where 1 represents never tired and 5 represents almost always tired in the past week. It will be measured at baseline, 6 weeks, and 12 weeks.*Self-efficacy* will be assessed by using the Children’s Arthritis Self-Efficacy Scale (CASE), a specific, valid and reliable tool for JIA [71]. CASE is an 11-item self-report scale that is divided into 3 concepts: activity, symptom, and emotion. A 5-point Likert scale is used to rate responses for each item, where 1 represents not at all sure and 5 represents very sure based on the confidence of the child to manage disease effects. It will be measured at baseline, 6 weeks, and 12 weeks.*Patient Global Assessment* will be assessed by using an item used in the Juvenile Arthritis Quality of Life Questionnaire (JAQQ). JAQQ was designed to assess HRQOL in children aged 2 to 18 years JIA or juvenile spondylarthritides [72-75]. JAQQ includes 4 subscales (gross motor function, fine motor function, psychosocial function, and systemic symptoms) as well as a pain and patient global assessment. The patient global assessment asks how youths have been since the last assessment (prior week) on a 5-point Likert scale, scored from 1 to 5, where 1 represents much better and 5 represents much worse. It will be measured at 6 weeks and 12 weeks.*Disease activity* will be assessed by using the active joint count, the number of joints with active disease according to the rheumatologist [1].Adverse events will be reported by participants in answers to open questions.

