**Methods:**

A three-arm prospective randomized open-label study with a parallel group design will be used. A total of 25 female adolescents with JIA who have pain will be randomized in a ratio of 2:2:1 to one of the 3 groups: (1) online yoga training program (group A: n=10); (2) online aerobic dance training program (group B: n=10); and (3) electronic pamphlet control group (group C: n=5). Participants in groups A and B will complete 3 individual 1-hour sessions per week using online exercise videos, as well as a 1-hour virtual group session per week using a videoconferencing platform for 12 weeks. Participants from all groups will have access to an electronic educational pamphlet on PA for arthritis developed by the Arthritis Society. All participants will also take part in weekly online consultations with a research coordinator and discussions on Facebook with participants from their own group. Feasibility (ie, recruitment rate, self-reported adherence to the interventions, dropout rates, and percentage of missing data), acceptability, and usability of Facebook and the videoconferencing platform will be assessed at the end of the program. Pain intensity, participation in general PA, morning stiffness, functional status, fatigue, self-efficacy, patient global assessment, disease activity, and adverse events will be assessed using self-administered electronic surveys at baseline and then weekly until the end of the 12-week program.

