### Study Design

This study will use a three-arm prospective randomized open-label study. Participants will be randomized to one of the 3 following groups in a ratio of 2:2:1: group A: an online yoga training program (and a PA electronic educational pamphlet; n=10); group B: an online aerobic dance training program (and a PA electronic educational pamphlet; n=10); and group C: an electronic pamphlet control group (PA electronic educational pamphlet; n=5). The total intervention period will be of 12 consecutive weeks. The frequency and duration of the interventions are based on other trials of yoga and PA interventions in pediatric and adult rheumatology [18,20,22,26,58]. As this pilot RCT involves physical interventions (ie*,* yoga and aerobic dance training programs), the participants and the research coordinator administering the program will not be blinded. However, the use of anonymous online self-reported questionnaires administered at baseline and postintervention will reduce potential detection bias. With training and standard operating procedures in place, it is anticipated that any performance bias due to not blinding will be minimized.

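### The dropout rate is defined per unit of trial time with no group-size denominator, so it cannot be compared across arms of 10, 10 and 5; the lower bound of the SUS range also needs a small correction

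*Protocol article*

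**What the plan says.** The Outcome Measures section opens its first list with "The following outcome measures will be used to answer the primary objective". Feasibility heads that list and is to be judged by recruitment, randomisation and adherence, "as well as protocol deviations, dropout rates, and percentage of missing data in the questionnaires".

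For dropout, the feasibility form is to record how many participants left, when, from which group and why. The rate itself is then fixed: "The number of dropouts in each group will be divided by the duration of the trial".

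The arms are unequal by design. Study Design says "Participants will be randomized to one of the 3 following groups in a ratio of 2:2:1", with 10, 10 and 5 participants planned in groups A (yoga), B (aerobic dance) and C (electronic pamphlet control). The abstract gives the same split of 25. On length, Study Design says "The total intervention period will be of 12 consecutive weeks", and the Time paragraph of the Discussion also gives the study duration as 12 weeks.

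The same list includes the System Usability Scale (SUS), once for Facebook and once for the videoconferencing platform. Both entries say "The SUS is composed of 10 items using a 5-point scoring system", with 1 as the lowest and 5 as the highest score for each question. Both then say "The total score ranges from 5 (low usability) to 50 (high usability").

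Data Analysis says only that dropout data will be collected. It neither repeats nor replaces the definition.

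**The concern.** A dropout rate in a pilot should say what share of those randomised to each arm was lost, or how fast people left per person followed. Either version needs the number of people at risk. The stated definition has no such term. Its divisor is the same for every arm, so the rate is the raw count on another scale.

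With equal arms this would be harmless for comparing them. With a 2:2:1 allocation it is not. Arms with very different proportional losses can show the same rate, and arms with the same proportional loss can show different rates. Anyone following the definition literally would report a misleading figure for each arm on a measure meant to inform a full-scale trial, whose planning needs the proportion lost per arm.

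Dividing by time suits the recruitment rate, which the same section defines as participants divided by the length of recruitment. It does not carry over to attrition. The adherence measure in that section has a proper denominator, namely the prescribed session time.

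The SUS point is smaller. The lower end of the printed range does not agree with the number of items and the item scores printed beside it.

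**Working it through.** **Inputs**
- Planned group sizes: A = 10, B = 10, C = 5 (abstract; Study Design).
- Duration: 12 weeks, common to all arms (Study Design; Discussion, Time).
- Stated dropout rate: d / duration, where d is the number of dropouts in the group (Outcome Measures).
- SUS: 10 items, each scored 1 to 5, printed total 5 to 50 (Outcome Measures).
- Expected dropout: not given. The values of d below are assumptions, shown over a range.

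**Dropout: same count in each arm**

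Stated rate = d/12. Proportion lost = d/n, with n the number randomised.

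| d | Stated rate, any arm (per week) | Lost in A or B (d/10) | Lost in C (d/5) |
|---|---|---|---|
| 1 | 1/12 = 0.083 | 10% | 20% |
| 2 | 2/12 = 0.167 | 20% | 40% |
| 3 | 3/12 = 0.250 | 30% | 60% |
| 5 | 5/12 = 0.417 | 50% | 100% |

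In every row the stated rate is identical across arms while the proportion lost in C is twice that in A or B. In the last row, losing the whole control group reads the same as losing half of an exercise group.

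**Dropout: same proportion in each arm**

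A 20% loss means 2, 2 and 1 participants. The stated rates are 2/12 = 0.167, 2/12 = 0.167 and 1/12 = 0.083 per week. The twofold difference comes only from the allocation ratio.

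Neither result depends on reading the duration as 12 weeks. Any common divisor cancels when arms are compared, so the ratio of stated rates is always the ratio of raw counts.

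**Dropout with a person-time denominator**

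For d = 2, dividing by the planned person-weeks gives 2/(10 × 12) = 0.0167 in A or B and 2/(5 × 12) = 0.0333 in C. The twofold difference reappears. Actual person-time would be somewhat lower, because people who leave stop contributing.

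**SUS range**

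Trying to reproduce the printed 5 to 50:
- Raw sum, items 1 to 5: 10 × 1 = 10 up to 10 × 5 = 50.
- Items recoded 0 to 4: 10 × 0 = 0 up to 10 × 4 = 40.
- Item mean: 1 to 5.

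None gives 5 to 50. The printed maximum agrees with the raw sum. The printed minimum does not, because the lowest possible raw sum is 10.

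**The case against.** The strongest reply is that nothing is lost. The feasibility form records dropouts by group with timing and reasons, the number randomised will be known, and Data Analysis names proportions among its descriptive statistics. Any reader could work out the proportion per arm. This stands, and it limits the severity. It does not make the definition right: the mention of proportions is a general statement about baseline and end-of-study variables, and the only formula given for dropout is the one that omits group size.

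A reader might go further and infer that the faulty rate could tip the decision on a full-scale trial. The article does not support that, since it states no progression threshold and no between-arm test that uses dropouts per week. Nor is there much in the complaint that the figure would change with the length of the trial. The length is fixed, and a cumulative proportion also depends on follow-up.

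For the SUS, a reader might infer that the scoring is wrong or that usability will be misjudged. The article supports neither. The error lies in a printed bound. Observed totals are the same whether the minimum is printed as 5 or 10, and no cut-off or percent-of-range conversion is stated.

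**Conclusion.** The dropout definition is wrong as written and should be fixed. It is a count over a constant, so with planned arms of 10, 10 and 5 equal stated rates correspond to a twofold difference in proportional loss, and equal proportional losses produce a twofold difference in stated rates. This holds for any number of dropouts and any common duration; it rests only on the planned 2:2:1 sizes. The particular counts used are illustrations.

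The fault is one of definition. It does not prevent the pilot from measuring attrition, because the necessary data are already to be collected, and no stated decision rule depends on the rate.

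The SUS lower bound is a minor correction: 10 in place of 5, at the two places where it appears. The upper bound of 50 is consistent with the stated scoring.

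**What to change.** - **Dropout.** Define the rate as the number who withdrew by week 12 divided by the number randomised in that arm. Dropouts per person-week of follow-up would be a valid alternative. Report time to dropout separately.
- **Precision.** An exact 95% confidence interval beside each proportion is preferable in arms this small: 2/10 gives about 3% to 56%, and 2/5 about 5% to 85%. This is a recommendation; leaving intervals out of the article is not itself a fault.
- **SUS.** Change the stated minimum total from 5 to 10 for both Facebook and the videoconferencing platform.

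The cost is a change of wording and of one line in the summary calculations, with no new data. The article reports that recruitment and data collection had not started as of May 11, 2020, so at that date the definition could be corrected before any results were seen.

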### Objectives

The primary objectives of the proposed single-blind three-arm pilot RCT with a parallel group will be to examine (1) the feasibility of a 12-week full-effectiveness trial of two popular types of PA and an electronic pamphlet control group: group A: an online yoga training program and a PA electronic educational pamphlet; group B: an online aerobic dance training program and a PA electronic educational pamphlet; group C: an electronic pamphlet control group (PA electronic educational pamphlet) postintervention; and (2) the acceptability of the yoga and aerobic dance PA interventions. The secondary objective of this pilot RCT will be to examine the initial effectiveness of a yoga training program (group A) and an aerobic dance training program (group B) on pain intensity, participation in PA, morning stiffness, functional status, self-efficacy, fatigue, patient global assessment, disease activity, and adverse events in female adolescents (aged 13 to 18 years) with JIA compared with an electronic pamphlet control group (group C) postintervention.

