### Outcomes

The feasibility of a full trial will be monitored throughout the study (eg*,* randomization, recruitment and retention of participants, data collection, and self-reported adherence). The acceptability of the interventions will be assessed using online questionnaires at the end of the study.

Clinical outcomes will be evaluated at baseline, weekly, and postintervention (at 12 weeks) through the use of online questionnaires in REDCap (Vanderbilt University). At baseline, pain intensity, functional status, fatigue, and self-efficacy will be assessed. Pain intensity and fatigue will be monitored weekly. Finally, all of these outcomes as well as the patient’s global assessment will be assessed postintervention. Outcomes were selected based on a JIA core set of outcomes to assess in trials [59]. Outcomes that were found to be essential include pain, functional status, patients’ overall well-being (global assessment), joint inflammation signs, and adverse events [59]. Other outcomes that were found to be important but not essential include fatigue, joint stiffness, and PA [59]. Other outcomes need more research to be endorsed, such as coping with the illness, which is related to self-efficacy [59].

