Participants will be invited via Facebook and email to attend an individual online consultation with the research coordinator using a videoconferencing platform. During this consultation, participants can ask questions related to their group assignment, voice their concerns, and establish a plan of action. For the remainder of the study duration, participants will be encouraged to attend, when possible, individual 10-minute online consultations weekly. During these consultations, participants can provide their feedback and discuss their use of the PA program as well as facilitators and barriers to participating. Private meetings are less difficult to schedule than group meetings and provide greater privacy. They may also be more motivating and less intimidating for participants who may feel their voice really matters and has an impact.For the study duration, participants will be asked to complete 3 individual exercise sessions as well as 1 virtual group session each week. The links to the videos will be posted on Facebook and sent by email for participants to use for their individual exercise sessions. For group sessions, the videoconferencing platform link will be posted on Facebook and sent to participants via email. Virtual group sessions will help ensure that they perform the exercises that they observe in the video safely and that they do not hurt themselves. They will also be able to see other participants and be seen if they wish, which will be a motivating factor to perform the PA. A schedule of virtual group sessions offered in the morning or afternoon will be posted on the Facebook group page or sent by email.Participants will be asked to record their PA using a validated exercise log [61] as well as their pain intensity and fatigue by completing a brief online questionnaire that regroups valid instruments on a weekly basis. They will be reminded to do so via Facebook, email, and during their online consultations.

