#### Outcomes

Assessments will include a range of clinical outcome measures validated in JIA. Although pain and other outcomes are self-reported, they represent important unwanted symptoms that have functional consequences that affect the activities of daily living of youths with JIA. Furthermore, objective measures of these symptoms are difficult to obtain. However, it is important to be mindful that self-reported measures may lead to reporting bias.

There is also the potential to include further measurements such as PA level (using a questionnaire or an accelerometer) and aerobic exercise testing (ie*,* assessment of submaximal oxygen consumption: PWC_170_, physical working capacity at a heart rate of 170 beats per min) to determine potential differences between treatment arms in the full-scale RCT.

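### Girls who leave before week 6 never rate acceptability, and adherence rests on self-report although 12 of 48 prescribed sessions could be observed

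*Protocol article*

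**What the plan says.** **Status of the two measures.** The Objectives section lists as a primary objective "2) the acceptability of the yoga and aerobic dance PA interventions". Adherence also serves the primary objective: "Feasibility will be assessed by the recruitment rate, the randomization process, and self-reported adherence and measured using a questionnaire".

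**Acceptability.** Outcome Measures says "The acceptability of the yoga or aerobic dance interventions will be assessed using a questionnaire-administered postintervention". A little further on, about the same instrument, it says "This questionnaire will be administered at 6 and 12 weeks". Participant Allocation agrees with weeks 6 and 12 and asks all participants. The Outcomes section of the Methods says instead "The acceptability of the interventions will be assessed using online questionnaires at the end of the study", and the Abstract also puts the assessment at the end of the programme.

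**Adherence.** It is time spent on the programme divided by prescribed time. Its source is stated in Outcome Measures: "Self-reported adherence will be recorded weekly using an adapted online version of the validated 7-day PA Report calendar (in minutes".

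**Live sessions.** Groups A and B have three individual sessions and one virtual group session a week for 12 weeks. On access to the latter, Participant Allocation says "For group sessions, the videoconferencing platform link will be posted on Facebook and sent to participants via email". Attendance at these sessions is not named as a measure. The only outcome listed for the videoconferencing platform is the System Usability Scale.

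**What else is collected.** Outcome Measures records the number, timing, group and reasons for dropouts, the percentage of missing questionnaire data, and counts of posts, live discussions and video views on Facebook.

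**The concern.** Acceptability and adherence are among the measures that tell the investigators whether these programmes suit a full-scale trial. A girl who leaves in week 3 because the sessions are too long is asked why she left. She is never asked to rate the consultations, group sessions, videos, pamphlet, content or duration, which are the items of the acceptability questionnaire. If early leavers are the less satisfied participants, their views are missing from the result for primary aim 2.

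Adherence has a different weakness. In groups A and B, participants report their own minutes and also discuss their use of the programme with the research coordinator each week, which is a plausible source of over-reporting. The plan compares those minutes with nothing independent, although one session in four takes place live in a group.

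Both features would tend to favour a conclusion that the programmes are acceptable and followed. Neither can be repaired at the analysis stage, because ratings and attendance that were not collected cannot be recovered.

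**Working it through.** The article gives no expected acceptability, adherence or dropout rate, so there is no stated figure to reproduce. The check has three parts: who is missed, how much that could matter, and what could be observed.

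**1. Who is missed on acceptability**

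| Place in the article | Timing stated |
|---|---|
| Abstract, Methods | end of programme |
| Outcomes (Methods) | end of study |
| Outcome Measures, opening sentence of the item | postintervention |
| Outcome Measures, closing sentence of the item | weeks 6 and 12 |
| Participant Allocation | weeks 6 and 12 |

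Under weeks 6 and 12, those missed are leavers before week 6 and non-responders. Under an end-only schedule, everyone who leaves before week 12 is missed. The gift certificates (US $21.40 each) are for the baseline and postintervention questionnaires, so no stated incentive supports a reply at week 6 or at withdrawal.

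**2. Illustrative size for acceptability (assumed inputs)**

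Groups A and B have 10 + 10 = 20 participants, so each missing girl is 1/10 = 10 percentage points of her arm, or 1/20 = 5 points of the two combined. Let d be the fraction with no rating, p the acceptance among responders and q the acceptance that the missing would have given. Then

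all-randomised acceptance = (1 − d)p + dq, and a responders-only figure differs from it by d(p − q).

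Assume p = 0.80 and d = 0.20:
- q = 0: 0.80 × 0.80 + 0 = 0.64, so responders-only overstates by 16 points.
- q = 0.80: 0.64 + 0.16 = 0.80, no difference.
- q = 1: 0.64 + 0.20 = 0.84, so responders-only understates by 4 points.

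With q = 0 and d from 0.10 to 0.40, the overstatement is 0.80d, that is 8 to 32 points. With q = 1 over the same range, the understatement is 0.20d, that is 2 to 8 points. The sign therefore depends on q, which the planned data do not supply for early leavers.

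**3. Adherence**

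Prescribed sessions: (3 + 1) × 12 = 48. Live group sessions: 1 × 12 = 12, and 12/48 = 25%. The other 36 sessions use recorded videos.

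Leavers do contribute here, because the calendar is weekly. What they contribute depends on the denominator, which the article does not spell out. Assume 16 stayers at 75% and 4 leavers who stop at week 6 after 50%:
- completers only: 75.0%
- reported weeks only: (16 × 12 × 0.75 + 4 × 6 × 0.50)/(16 × 12 + 4 × 6) = 156/216 = 72.2%
- all prescribed weeks, zero after leaving: 156/(20 × 12) = 156/240 = 65.0%

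Counting all prescribed weeks removes the dropout part. It does nothing about over-reporting by those who do report. If, say, girls reported 80% when true completion was 60% (again assumed), every denominator would carry that error, and the named adherence data contain no independent check on it.

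**The case against.** The strongest reply is that the plan collects more than this point might suggest. Adherence is logged weekly, so leavers contribute until they go. Acceptability is asked of all participants at week 6, so someone leaving later may already have answered. Leavers give reasons, missing data are reported as an outcome in their own right, weekly consultations invite feedback, and video views are a trace of use that is not self-reported. The adherence measure is openly labelled self-reported, and the Discussion concedes that "it is important to be mindful that self-reported measures may lead to reporting bias". The article also condenses a fuller protocol, which may hold denominators and missing-data rules.

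Much of this stands. A reader might infer that both measures come only from participants who stay, and that both are therefore biased upward. The documents do not support that. The weekly log and the week-6 questionnaire contradict the first part. The second needs leavers to be less accepting, or a denominator that excludes them, and the article fixes neither. It also defines no binary acceptable rating and no responders-only summary. The unstated denominators are not held against the plan, since they may sit in an analysis plan that is not shown.

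What remains is narrower. A reason for leaving is not a set of ratings. Video views are counted as use of Facebook and are not tied to adherence; study usernames omit real names and some participants will not use Facebook, so the counts cannot readily be linked to individuals. The conceded reporting bias comes with no check. The objection is also right that the platform is unnamed and nothing says it keeps a log, so the remedy should not depend on one.

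**Conclusion.** The point holds in limited form. On the article's more generous schedule, participants who leave before week 6 supply no acceptability ratings, and on its other wording nobody who leaves before the end does. Adherence is self-report only, while a quarter of the prescribed sessions could be observed. Both results are likely, not certain, to look more favourable than they are.

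The size is unknown. The figures of 64% to 84% for acceptability and 65.0% to 75.0% for adherence rest entirely on assumed rates and serve only to show that, with 10 girls per arm, a few early leavers can matter. The expectation of upward rather than downward error rests on two judgements outside the article's data: that early leavers tend to be less satisfied, and that minutes discussed with a coordinator tend to be over-reported.

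This is a cheap improvement to data collection, not a defect that invalidates the pilot. The article states that recruitment had not begun as of May 11, 2020, so the change could be made before any data were collected.

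**What to change.** 1. **Acceptability.** Offer the same questionnaire at withdrawal. State one schedule for it and use it in the Abstract, Outcomes, Participant Allocation and Outcome Measures. Report the number responding out of all randomised to group A or B, with a sensitivity summary for non-responders that shows how far the result could move in either direction.

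2. **Adherence.** Have the session host record who attends each weekly virtual group session, or use a platform log if one exists. Report sessions attended out of 12 beside self-reported adherence. Describe it as a partial check: it covers 12 of 48 sessions, and being connected is not verified exercise, particularly as participants need not be seen on camera.

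The cost is one short form for leavers, a little weekly record keeping, and possibly less favourable figures.
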